# SUMMARY

| **Title** | A Double-blind, Randomized, Controlled Phase IIb Field Trial in 12 to 47 Month-old Children in Western Kenya to Evaluate the Efficacy, Safety, and Immunogenicity of the FMP1/AS02A Malaria Vaccine (WRAIR’s MSP-1 Malaria Antigen Adjuvanted in GlaxoSmithKline Biologicals’ AS02A) Versus Rabies Vaccine |  |
| --- | --- | --- |
| **Study Population** | Healthy 12- to 47-month-old, malaria-exposed children |  |
| **Study Site** | The Walter Reed Project Kombewa Clinic in Kombewa Division, Kisumu District, Nyanza Province, western Kenya (and 12 small field stations within Kombewa Division) |  |
| **Objectives** | ***Primary***   - To assess the efficacy of the FMP1/AS02A malaria vaccine on clinical episodes of *P. falciparum* malaria during the Efficacy Follow-up Period (EFP)   ***Secondary (Efficacy)***   - To assess the efficacy of the FMP1/AS02A malaria vaccine against clinical episodes of *P. falciparum* malaria of differing severity during the EFP   ***Secondary (Safety and Immunogenicity)***   - To assess solicited adverse events occurring in the seven days following each dose of vaccine - To assess unsolicited adverse events occurring in the 30 days following each dose of vaccine - To assess serious adverse events occurring after the first dose of vaccine to the end of the EFP - To assess the immunogenicity of the FMP1/AS02A malaria vaccine from the first dose of vaccine to the end of the EFP - To assess the association between MSP-1 antibody titers and the subsequent risk of clinical malaria during the EFP   ***Tertiary (Safety and Immunogenicity)***   - To assess the safety of the FMP1/AS02A malaria vaccine during the Addendum Efficacy Follow-up Period (AEFP) - To assess the immunogenicity of the FMP1/AS02A malaria vaccine during the AEFP   ***Tertiary (Efficacy and Exploratory)***   - To assess the efficacy of the FMP1/AS02A malaria vaccine against clinical episodes of *P. falciparum* malaria during the AEFP - To assess the biological effects of the FMP1/AS02A malaria vaccine during the AEFP |  |
|  |  |  |
| **Test Vaccine** | 50 g of lyophilized FMP1 antigen reconstituted with 0.50ml of AS02A adjuvant |  |
| **Comparator Vaccine** | Rabies vaccine |  |
| Immunization Schedule | 0, 1, and 2 months (Provisionally: Study Days 0, 29, and 57) |  |
| Route of Administration | IM injection into left anterolateral thigh muscle |  |
| Number of Subjects | Four hundred (400) subjects of either gender will be enrolled and randomized 1:1 to FMP1/AS02A or rabies vaccine |  |
| Study Duration | Enrollment is expected to be completed within 7 to 10 days; however, it may continue for up to an additional 15 (for a total of 25 days) if the desired number of subjects has not been enrolled by the end of the 10th vaccination day. Once enrolled, each subject will be followed for 12 months. Total study duration will be about 14 months. |  |
| **Primary endpoint** | Measurement of clinical efficacy of the vaccine, during the efficacy follow-up period (EFP), as determined by time to first clinical episode of *P. falciparum* malaria meeting the primary case definition |  |
| **Secondary endpoints** | Measurements of efficacy during the EFP:   - Times to clinical episode of *P. falciparum* malaria meeting the various secondary case definitions shown in Exhibit 8 - Time to presence of asexual stage *P. falciparum* parasites during the six-month efficacy follow-up period - Time to parasite density  50,000 asexual stage *P. falciparum* parasites per microliter of blood during the six-month efficacy follow-up period - Number of clinical episodes of malaria, per subject, meeting the primary case definition - Presence of MSP-1 3D7 parasites in clinical cases of malaria meeting the primary case definition - Presence of MSP-1 3D7 parasites at a given cross-section survey time - Time to anemia defined as Hgb < 8.0 g/dl, whether by active or passive case detection - Proportion of subjects with anemia (Hgb < 8.0 g/dl)   Safety during the EFP:   - Occurrences of solicited AEs during a seven‑day follow-up period (vaccination day and six subsequent days) after each vaccination (five visits: vaccination day and days 1, 2, 3, and 6) - Occurrences of unsolicited AEs during a 30-day follow-up period after each vaccination (vaccination day and 29 subsequent days) - Occurrences of SAEs between the first vaccination and the end of the EFP   Immunogenicity during the EFP:   - Geometric means of MSP-1 Ab titers at Visits 2, 7, 12, 17, 20, and 23 (o/a Study Days 0, 29, 57, 85, 171, and 256) |  |
| **Tertiary Endpoints** | Measurement of safety (during the EFP and Addendum Efficacy Follow-up Period [AEFP]):   - Occurrences of SAEs between the first vaccination and the end of the study   Measurement of immunogenicity (during the EFP and AEFP):   - Geometric means of MSP-1 Ab titers at Study Days 0, 29, 57, 85, 171, 256, and 340   Measurement of efficacy and other biological effects by either active or passive detection (during the AEFP unless otherwise noted):   - Times to first clinical episode of *P. falciparum* malaria meeting the primary case definition (EFP and AEFP combined) - Times to first malaria episode of *P. falciparum* malaria meeting the secondary case definitions in Exhibit 8 (EFP and AEFP combined) - Time to presence of asexual stage *P. falciparum* parasites (EFP and AEFP combined) - Time to parasite density  50,000 asexual stage *P. falciparum* parasites per microliter of blood (EFP and AEFP combined) - Number of clinical *P. falciparum* malaria episodes, per subject, meeting the primary case definition (EFP and AEFP combined) - Presence of MSP-1 3D7 parasites in clinical cases of malaria meeting the primary case definition (EFP and AEFP combined) - Presence of MSP-1 3D7 parasites at a given cross-section survey time (EFP and AEFP combined) - Vaccine-induced GIA activity - The parasite density at each episode of malaria infection meeting the primary and secondary definitions of clinical malaria and infection (see Exhibit 8) - *P. falciparum* malaria allele types per malaria episode, meeting the primary and secondary definitions of clinical malaria and infection (see Exhibit 8) - Times to first observation of anemia (Hgb < 8.0 g/dl), whether by active or passive case detection (EFP and AEFP combined) - Hgb levels at all scheduled points of collection - Proportion of subjects with anemia (Hgb < 8.0 g/dl) at all scheduled points of hgb collection - Proportion of subjects with a documented decline in Hgb level of ≥ 20% - Proportion of subjects with anemia (Hgb < 8.0 g/dl) at last scheduled study hgb collection - Number of cases of documented decline in Hgb level from baseline to last study sample collection - Parasite density at all scheduled points of collection - Non-3D7 parasite densities at all scheduled points of collection - Genotyping for multiplicity of infections - Antibody against fragments of MSP-142 - Antibody able to compete for binding to recombinant MSP-142 - Antibody able to inhibit secondary processing of MSP-142 |  |

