**Days 1-3 Daily Post- vaccination 1 follow-up visits**

***Visits 3-5***

- Record pulse, axillary temperature
- Examine site of injection
- Record solicited and unsolicited AEs
- History-directed general physical examination
- Check concomitant medications

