**Day 6 ± 3 Day 6 Post- vaccination 1 follow-up visit**

***Visit 6***

- Record pulse, axillary temperature
- Examine site of injection
- Record solicited and unsolicited AEs
- History-directed general physical examination
- Check concomitant medications

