**Day 35 ± 3 Day 6 Post - vaccination 2 follow-up visit**

***Visit 11***

- Record pulse, axillary temperature
- Examine site of injection
- Record solicited and unsolicited AEs
- HIstory-directed general physical examination
- Check concomitant medications

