**Day 63 ± 3 Day 6 Post- vaccination 3 follow-up visit**

***Visit 16***

- Record pulse, axillary temperature
- Examine site of injection
- Record solicited and unsolicited AEs
- History-directed general physical examination
- Check concomitant medications

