| **Cumulative** Blood Vol. (ml) | 2 | 5 | 5 | 8 | 8 | 11 | 11 | 14 | 16 | 18 | 20 | 22 | 24 | 26 | 27j |  |

1. Days/dates for doses 2 and 3 are for planning purposes and are provisional only.
2. Performed within 45 days prior to randomization.
3. Blood collected just before immunization.
4. Limited to Hgb, WBC, RBC, lymphocytes, platelets.
5. Serum for MSP-1 antibodies collected on Study Days 171, 256, and 340.
6. Pre-dose and 60 min after each dose.
7. Solicited symptoms collected on Study Days 0, 1, 2, 3, and 6 after each dose. Unsolicited AEs collected from SD 0 through 85.
8. Concomitant medications collected from Study day -7 through 364.
9. Monthly field worker visits to checkaxillary temps, history of fever, and location and general status of subjects.
10. Volume does not include that taken for repeat screenings (if necessary) or for diagnostic samples in case of illness.
11. Includes history of malaria prevention methods used by the subject.
12. Includes death, out-migration, absences from Kombewa, and antimalarial drug usage.
13. Collected if temp ≥ 37.5°C, or if history of fever in previous 24 hours.
14. Age, sex, bed net use, nearest field site station, Hgb genotype.

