### Unsolicited Adverse Events

A CRF will be provided to record unsolicited AEs. Unsolicited AEs are signs or symptoms reported by the subjects or their parents within 30 days of a vaccination that are different from those solicited symptoms recorded during the seven-day post-vaccination follow‑up period. Signs and symptoms that would fit the solicited AE category, but actually start after the sixth day post-vaccination, will also be considered unsolicited AEs. An investigator will ensure that any general (systemic) signs or symptoms reported will be evaluated, and their relationship with the study vaccine determined and transcribed onto the CRF.

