### Analysis of Safety

The overall percentage of subjects with at least one local AE (solicited and unsolicited) and the percentage with at least one general AE (solicited and unsolicited) during the seven-day follow-up period after vaccination will be tabulated. The incidence, intensity, and relationship of individual solicited symptoms over a seven-day period of follow‑up (day of vaccination, plus days 1, 2, 3, and 6) will be calculated for each study arm.

The number of subjects with at least one report of unsolicited AE reported up to 30 days after vaccination will be tabulated by study arm. The intensity and relationship to vaccination of the unsolicited symptoms reported will also be assessed.

SAEs are expected to be rare, but where observed will be described. Analysis of safety during the 12-month follow-up period (ten months after dose 3) will consist of comparison of incidence of SAEs as well as of changes in mean hemoglobin levels.

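### The last solicited-AE visit after each dose has two conflicting tolerances (± 3 and ± 9 days), and under either one an early visit can leave up to days 4-6 of the seven-day endpoint after the last scheduled solicited assessment

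*Protocol*

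**What the plan says.** **Endpoint period.** The Summary and Section 12.1.2 count solicited events over "vaccination day and six subsequent days) after each vaccination (five visits: vaccination day and days 1, 2, 3, and 6". Section 12.4.4 analyses the same period: "day of vaccination, plus days 1, 2, 3, and 6) will be calculated for each study arm". The Exhibit 7 footnote agrees and gives no tolerance: "Solicited symptoms collected on Study Days 0, 1, 2, 3, and 6 after each dose". Section 10.1.3 limits elicitation to the first six days after immunization.

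**Visit timing in Section 7.2.** The early visits have no tolerance: "Days 1-3 Daily Post- vaccination 1 follow-up visits". The last visit does, at every dose:
- Visit 6: "Day 6 ± 3 Day 6 Post- vaccination 1 follow-up visit"
- Visit 11: "Day 35 ± 3 Day 6 Post - vaccination 2 follow-up visit"
- Visit 16: "Day 63 ± 3 Day 6 Post- vaccination 3 follow-up visit"

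**Visit timing in Exhibit 6.** The intervals from Visit 2 to 6, Visit 7 to 11 and Visit 12 to 16 are each listed as 6 ± 9 days.

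**Classification.** Under Section 10.1.6, signs that would fit the solicited list "but actually start after the sixth day post-vaccination, will also be considered unsolicited AEs".

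**The concern.** One visit cannot have two tolerances, and neither of the two fits inside the day 0-6 period that the visit is meant to close. The day 6 visit is the only scheduled solicited assessment after day 3, so its timing decides whether days 4-6 are covered.

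At stake is absolute ascertainment, more than the comparison between arms. Section 12.4.4 reports incidence and intensity over the seven-day period. The Section 6.9.2 report before the next dose covers the same seven days. Section 6.9.1 suspends vaccination on a pooled, blinded count of children (20 or more, 5%) with related Grade 3 solicited systemic events. If days at the end of the period go unassessed, these figures can fall but cannot rise.

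**Working it through.** The check is day counting, with vaccination as day 0.

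**Inputs.** Endpoint days 0-6 and visits on days 0, 1, 2, 3 and 6 (Summary, Sections 12.1.2 and 12.4.4). Visit 5 on day 3 with no tolerance, and the last visit at ± 3 (Section 7.2). The last visit at ± 9 (Exhibit 6).

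**Step 1. Reproduce the plan's own figures.** Days 0 to 6 make 7 days, and {0, 1, 2, 3, 6} makes 5 visits. The nominal day 6 after doses 2 and 3 is 29 + 6 = 35 and 57 + 6 = 63, which match the Visit 11 and Visit 16 headings. The nominal schedule is consistent.

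**Step 2. Range allowed by each tolerance.**
- ± 3: 6 − 3 = 3 to 6 + 3 = 9, so days 3 to 9 (7 possible days). Day 3 coincides with Visit 5, and days 7, 8 and 9 fall after the period.
- ± 9: 6 − 9 = −3 to 6 + 9 = 15, so days −3 to 15 (19 possible days). Three precede the vaccination, 7 fall on or before day 3 (these include the three), and 9 (days 7 to 15) fall after the period.

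**Step 3. Endpoint days left after the last solicited visit,** with Visit 5 held on day 3:

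| Last visit on day | Endpoint days after it | Share of 7 |
| --- | --- | --- |
| 3 (or earlier, under ± 9) | 4, 5, 6 | 3/7 = 43% |
| 4 | 5, 6 | 2/7 = 29% |
| 5 | 6 | 1/7 = 14% |
| 6 or later | none | 0 |

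The maximum is 3 days under both tolerances, because Visit 5 covers up to day 3 in any case. A visit on day 6 or later leaves no endpoint day after it. Days 4 and 5 then rest on recall even when the visit is exactly on day 6.

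**Step 4. Would a later contact close the gap?** Section 10.1.3 lets any undocumented event be recorded at any later encounter. The scheduled encounters help little:
- The next routine contact is a field-worker home visit. Section 7.2 limits it mainly to temperature, 24-hour fever history, medications and tracking, and Exhibit 7 leaves its adverse-event row blank (only serious events are marked).
- After dose 1, the next scheduled clinic assessment of adverse events is Visit 7 at day 29 ± 9, so day 29 − 9 = 20 at the earliest.
- After dose 3, it is Visit 17 at Study Day 85 ± 10. With dose 3 on Study Day 57 that is 85 − 10 − 57 = 18 days after the dose at the earliest.
- The missed-visit rule in Section 7.1.3 asks only about the previous 24 hours.

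**The case against.** The strongest reply is that this is a slip in one table. Day 6 is clearly the intended day. Section 16.3.3 staffs the follow-up centers on Study Days 6, 35 and 63 exactly. The largest gap arises only if Visit 6 is held on the same day as Visit 5, which defeats the five-visit schedule. Section 10.1.2 requires all events within 30 days of a dose to be recorded, Section 10.1.3 records onset and accepts late entries, and ill children can reach a field station at any hour. In Mal-031, with this vaccine, local symptoms resolved within 48 to 72 hours and general symptoms within 24 to 48 hours, so few events may begin on days 4-6. Both tolerances apply to both blinded arms.

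Most of this stands, and it makes the point minor. It does not say which tolerance governs, and the later contacts are a weak substitute for a solicited assessment (Step 4).

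Three stronger readings are tempting, and the documents do not support them:
- *Three incompatible timings.* Day 6 is the nominal day and is compatible with day 6 ± 3. The conflict is between two tolerances.
- *Unobserved days are scored as event-free.* A reader might infer this because Section 12.2.3 admits any dosed child with any safety data and Section 12.4.4 states no completeness condition. No passage gives such a scoring rule, and Section 12.4 leaves fuller analysis detail to a Reporting and Analysis Plan that is not at hand.
- *A sign is filed as solicited or unsolicited according to the visit date.* Section 10.1.6 goes by when the sign starts. A late visit lengthens recall but does not change the category.

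**Conclusion.** The point holds in a limited form and is minor. Visits 6, 11 and 16 have contradictory tolerances in Section 7.2 and Exhibit 6, and the Exhibit 6 lower limit is impossible. Either tolerance permits an on-schedule visit that leaves one to three of the seven endpoint days (14% to 43%) after the last scheduled solicited assessment. The effect on absolute solicited-AE incidence and on the pooled Grade 3 count can only be downward.

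This assumes that Visit 5 takes place on day 3 and that events on days 4-6 are not reliably picked up at later contacts. The number of children affected cannot be estimated from the protocol. The 400 × 3 = 1,200 planned dose periods are a ceiling, since an early visit is permitted but not planned. No bias between arms is shown, and the primary efficacy endpoint is untouched.

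**What to change.** Reconcile the Visit 6, 11 and 16 headings in Section 7.2 with the three matching rows of Exhibit 6, so that one window applies. That window should not let the last solicited assessment close before the day 0-6 endpoint period ends. Add to the safety reporting, by arm and dose, the number of children whose last solicited assessment fell before day 6, so that a reader can judge how complete the seven-day figures are. Onset-based classification and recording of onset need no change, because Sections 10.1.3 and 10.1.6 already provide them.

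The cost is a few words in four places and one extra count per arm and dose, derived from visit dates already collected. Removing the early side of the window gives the clinic slightly less scheduling freedom.

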
# INTRODUCTION AND BACKGROUND

## Life Cycle of the Malaria Parasite

The malaria parasite has a complex life cycle. The bite of an infectious mosquito transmits the sporozoite form of the parasite to humans. These sporozoites travel through the bloodstream and ultimately invade liver cells where they multiply asexually as exoerythrocytic stage parasites. The exoerythrocytic forms of *Plasmodium falciparum* mature in five to seven days releasing thousands of tissue merozoites that invade erythrocytes and initiate the erythrocytic phase of the infection. The free merozoites invade erythrocytes, undergo asexual maturation, and ultimately rupture the erythrocytes releasing new merozoites. This phase, characterized by cyclic destruction of erythrocytes, results in the clinical disease known as malaria. A small number of the invading merozoites do not multiply, but instead differentiate into sexual forms known as gametocytes. When ingested by a female mosquito, male and female gametocytes unite to form a zygote, which then matures to release sporozoites which subsequently migrate to mosquito salivary glands where they are available to infect the next person bitten, thus completing the parasite’s life cycle.

## Status of Merozoite Stage Malaria Vaccines

Malaria is a major worldwide problem with transmission occurring throughout Africa, Asia, Oceania, and Latin America. Over two billion people are estimated to live in malarious areas of the world. In Africa, for example, an estimated 300 to 500 million cases of malaria occur each year (1). Between 700,000 and 2.7 million people die from malaria each year; the majority are African children (2, 3). The sub-Saharan African region accounts for 90% of the disease burden which affects mainly children below five years old. About 75% of the 550 million people in Africa live in areas of highly endemic stable transmission. Another 18% live in epidemic‑prone areas where malaria transmission is seasonal and unstable, with all age groups being vulnerable to infection and disease (4). Between 400 and 900 million acute febrile episodes occur yearly in African children under five years of age living in endemic areas. Although about half of these children are not parasitemic, all merit consideration for malaria-specific therapy. Fewer than 20% of febrile episodes and deaths come to the attention of any formal health system. The relatively few ill patients who have any contact with the health services represent the “ears of the hippopotamus” (2); the majority of the patients receive minimal or no medical attention (4). *P. falciparum* causes about 80% of the infections and practically all the severe forms of malaria and deaths.

The objective of developing an effective malaria vaccine has been a major focus of malaria research for many years. This task has proven more difficult than initially thought. To date, no highly effective malaria vaccine is on the horizon in spite of considerable progress. Several lines of evidence show that blood stage immunity is both important and achievable. Adults living in areas of high malaria transmission become relatively resistant to malaria while continuing to become infected, suggesting that the immune response against antigens expressed during the blood stage may play a role. This has been corroborated by experiments where serum has been transfused from heavily exposed individuals to ill patients and the disease has been modulated. Moreover, the feasibility of impacting the parasite with a recombinant protein vaccine has been demonstrated in recent field trials in Papua New Guinea that showed parasite density was decreased in a vaccinated group (5).

Two critical steps of the malaria life cycle have been closely examined as potential targets for vaccine-induced immunity: 1) the invasion of hepatocytes by sporozoites and 2) the invasion of erythrocytes by merozoites. The merozoite stage of the parasite, like the sporozoite, is a logical target for a malaria vaccine because blockade of erythrocyte invasion would completely prevent clinical disease. Even if the vaccine were incapable of completely blocking merozoites from invading red blood cells, an immunologic reduction in the magnitude of parasitemia may significantly impact disease. Therefore, the identification of the molecular mechanisms of merozoite invasion of red blood cells has been an active area of investigation in the field of malaria vaccine research. Several antigens have been identified that have the potential to inhibit merozoite invasion of red cells. The most studied of these antigens, and also the most promising candidate as a constituent of a blood stage vaccine, is the merozoite surface protein 1 (MSP-1), a 195 kDa antigen found on the surface of merozoites. MSP-1 undergoes processing by proteolytic cleavage to a 42 kDa fragment and further to a 19 kDa fragment that has been implicated in the invasion of erythrocytes by the merozoite (6).

Several lines of evidence point to MSP-1 as a promising vaccine candidate. Antibodies directed against portions of MSP-1, in particular against the 19 kDa C-terminal fragment, inhibit erythrocyte invasion (6, 7). At least one field study has demonstrated an association between the presence of antibodies against MSP-1 and resistance to clinical malaria (8). Immunization with recombinant fragments of this molecule also protects non-human primates against *P. falciparum* (9) when used with Complete Freund’s Adjuvant, and mice against *P. yoelii* (10, 11). Passive transfer of immune sera in mice also confers protection (12). Although the weight of evidence indicates that antibodies against the C-terminal fragment of MSP-1 are protective, in one case immunization with C-terminal constructs did not result in protection (13). Lack of protection in some cases could be due to the use of antigenic constructs that lack a proper conformational structure because this region of MSP-1 is known to be conformationally dependent. In addition, vaccine efficacy is critically dependent on vaccine formulation. MSP-1 may also be the target of CD4+ T cells. Several T-cell epitopes have been identified (14, 15).

A recombinant version of the 42 kDa C-terminal portion of MSP-1 has been produced at the Walter Reed Army Institute of Research. This falciparum merozoite protein 1 (FMP1) is produced as a histidine-tagged (His6) fusion protein in *Escherichia (E.) coli*. The antigen, derived from the 3D7 clone of *P. falciparum*, contains both T-cell and B-cell epitopes. Monoclonal antibodies raised against native parasite MSP-1 recognize correctly folded conformational disulfide-bonded epitopes within the recombinant 42 kDa antigen. An efficient fermentation and purification process has been developed to produce this antigen on a scale compatible with industrial manufacture. The vaccine is formulated in the same adjuvant system used in the RTS,S vaccine, now called AS02A (the second ‘A’ denotes absence of thimerosal). To increase product stability, the MSP-142 antigen is manufactured as a lyophilized product and reconstituted just prior to injection.

As background, the “RTS,S” antigen is a recombinant protein based upon the *P. falciparum* CS protein covalently linked to the hepatitis B surface antigen. RTS,S when formulated with the adjuvant system AS02A, is a prototype malaria vaccine now undergoing field trials. Due to the more extensive experience with RTS,S/AS02A in children in malaria endemic populations, these data are summarized in the protocol as supporting evidence for the safety of a FMP1/AS02A formulation in children in Kenya.

The study proposed here is a Phase IIb efficacy study of FMP1/AS02A in a malaria‑endemic area of western Kenya. If this candidate vaccine proves efficacious and safe, further studies may be pursued with this same formulation to assess its efficacy singly or in combination with a pre-blood-stage antigen. Several trials have studied the antigen FMP1 and the adjuvant AS02A (see Exhibit 1).

Exhibit 1. Summary of clinical trials of FMP1 and AS02A

| **Study** | **Vaccine** | **Study population** | **Vaccine groups** | **Design (and results)** |
| --- | --- | --- | --- | --- |
| Mal-014 | FMP1/AS02A | 15 malaria-naïve adults at Walter Reed | 0.10, 0.25, 0.50 µg doses | Phase Ia open-label, dose-escalation. 0, 1, 3 month schedule |
| Mal-015 | RTS,S/AS02A | 6-11 year-old children in the Gambia | 0.10, 0.25, 0.50 µg doses  on a 0, 1 and 3 month schedule | Phase Ib trial |
| Mal-019 | FMP1/AS02A and RTS,S/AS02A | 71 malaria-naïve adults at Walter Reed | Four vaccine groups, 11 in challenge control: - FMP1/AS02A+RTS,S/AS02A at   separate sites of injection (n=15)  - FMP1/AS02A+RTS,S/AS02A at   one injection site (n=15)  - FMP1/AS02A (n=15)  - RTS,S/AS02A (n=15)  - Unvaccinated controls (n=11) | Phase I/IIa challenge study (Showed no interference between RTS,S/AS02A and FMP1; FMP1 alone did not prevent malaria) |
| Mal-020 | RTS,S/AS02A | 1-5 year-old children in the Gambia | 0.10, 0.25, 0.50 µg doses  on a 0, 1 and 3 month schedule | Phase Ib trial |
| Mal-024 | FMP1/AS02A vs. *Imovax®* Rabies | 40 malaria-exposed adults in western Kenya | Two study groups: - Full dose (0.50 µg) of FMP1/AS02A (n=20) - Imovax® Rabies (n=20) | Phase Ib to assess safety and immunogenicity. 0, 1, 2 month schedule (Vaccine deemed safe to perform Phase Ib trial in children) |
| Mal-025 | RTS,S/AS02A vs. *Engerix-B* (Hep B) | Sixty 1-4 year-old children in Mozambique | 0.25mL | Phase Ib safety & immunogenicity trial. 0, 1, 2 month schedule |
| Mal-031 | FMP1/AS02A vs. *Imovax®* Rabies | 135 1-4 year-old malaria-exposed children in western Kenya | Four study groups: - One-fifth dose (0.10 µg) of FMP1/AS02A (n=30);  - Half dose (0.25 µg) of FMP1/AS02A (n=30); - Full dose (0.50 µg) of FMP1/AS02A (n=30); - Imovax® Rabies (n=45). | Phase Ib trial to assess safety and immunogenicity and to decide on dose level for Mal-036. 0, 1, 2 month schedule  (Vaccine deemed safe to perform Phase IIb trial in children) |

